## Abstract

**Background:**

The number of middle-aged working individuals being diagnosed with cancer is increasing and so too will disruptions to their employment. The aim of the Working After Cancer Study is to examine the changes to work participation in the 12 months following a diagnosis of primary colorectal cancer. The study will identify barriers to work resumption, describe limitations on workforce participation, and evaluate the influence of these factors on health-related quality of life.

**Methods/Design:**

An observational population-based study has been designed involving 260 adults newly-diagnosed with colorectal cancer between January 2010 and September 2011 and who were in paid employment at the time they were diagnosed. These cancer cases will be compared to a nationally representative comparison group of 520 adults with no history of cancer from the general population. Eligible cases will have a histologically confirmed diagnosis of colorectal cancer and will be identified through the Queensland Cancer Registry. Data on the comparison group will be drawn from the Household, Income and Labour Dynamics in Australia (HILDA) Survey. Data collection for the cancer group will occur at 6 and 12 months after diagnosis, with work questions also asked about the time of diagnosis, while retrospective data on the comparison group will be come from HILDA Waves 2009 and 2010. Using validated instruments administered via telephone and postal surveys, data will be collected on socio-demographic factors, work status and circumstances, and health-related quality of life (HRQoL) for both groups while the cases will have additional data collected on cancer treatment and symptoms, work productivity and cancer-related HRQoL. Primary outcomes include change in work participation at 12 months, time to work re-entry, work limitations and change in HRQoL status.

**Discussion:**

This study will address the reasons for work cessation after cancer, the mechanisms people use to remain working and existing workplace support structures and the implications for individuals, families and workplaces. It may also provide key information for governments on productivity losses.

**Study Registration:**

Australian and New Zealand Clinical Trial Registry No. ACTRN12611000530921

## Background

Although cancer is often seen as a disease afflicting older people, each year in Australia over 40,000 cancers, or 43% of all cancers, are diagnosed in middle-aged people of working ages (45-64 years) [1] and the number of survivors living with cancer is increasing [2]. Consequently, research attention has turned to assessing health-related quality of life (HRQoL) and survivorship issues after a diagnosis of cancer.

One survivorship issue that is not well quantified is work participation and workplace issues after a diagnosis of cancer. Work can define a person's self-worth, identity and social purpose, and it contributes to financial security. A cancer experience that causes major disruption in the work role can become a source of high distress in addition to expensive medical bills, and can adversely affect HRQoL [3,4]. Inability to work may deprive an individual of stimulation, social contacts and independence, while staying in or returning to work after cancer treatment may be important for patients in maintaining a sense of normalcy and control [3,4]. Cancer treatments are improving and current treatments can involve prolonged periods of adjuvant therapy thus previous reports on the extent of disruption to work roles, earnings and other role activities may be outdated. Lengthy treatments, ongoing medical care or the experience of a recurrence may lead to reduced career options and loss of employment. Calls have therefore been made for oncology health workers to better recognise and screen patients for work-related distress [4].

Studies have shown between 30-93% of workers with cancer will return to work [5,6], with most people returning to work within 12 months of taking leave [5,6]. Survivors of head and neck cancer and breast cancer have shown more difficulty returning to work than survivors of other cancer types [5-7]. Although many people appear to resume their employment with minimal interference [8,9], there may also be difficult work re-entry, forced retirement, workplace discrimination and refusal of insurances [10]. Factors that have been linked with delayed return to, or stopping work include: older age [6,11,12]; physically-demanding work [5,6,9,12]; being female [5,6,11,12]; presence of comorbidities [5]; being married [6,11]; fatigue [13]; lower education [6,14]; chemotherapy [11]; blue collar occupations [11]; and upper-body limitations [9]. Amongst those who return to work, work disabilities are more common for those with a physically demanding job, advanced cancer stage and those experiencing treatment side-effects [4]. However, many of these studies are US-based and subject to a system of employment-based health insurance and the added pressure on individuals to keep working to retain access to health care services.

Current research concentrates on breast cancer survivors so the relevance for other cancer populations is unclear. A population-based cohort study of Australian colorectal cancer survivors assessed a subset of working adults for changes in work participation [15]. Twelve months after diagnosis, 33% of men (n = 621) and 40% of women (n = 354) were not working. Radiation therapy among men (OR = 1.90, 95%CI: 1.14- 3.17) and chemotherapy among women (OR = 1.87, 95%CI: 0.98-3.57) were associated with a higher prevalence of work cessation [15]. The risk of ceasing work among women was smaller if they had private health insurance (OR = 0.54, 95%CI: 0.31-0.92). Quality of life scores for persons who stopped working were significantly lower than for persons who continued working, after adjusting for additional explanatory factors [15]. However, this study was limited because there was no non-cancer comparison group and therefore was unable to determine the proportion of cases who would have ceased work irrespective of cancer.

This paper presents the protocol of a population-based observational study to examine the work experiences in adults with colorectal cancer. We aim to describe changes in work participation at two points in time within a 12-month period, identify the key predictors influencing work participation and time to work re-entry, quantify the extent of physical and cognitive limitations at work and the role of work on HRQoL. The results of the study will provide valuable information for individuals facing cancer, health professionals, supportive care services and government about the reasons for work cessation, the mechanisms people use to remain working and existing workplace support structures.

## Methods

### Study design

A longitudinal population-based study has been designed to enrol middle-aged (45-64 years) men and women newly-diagnosed with colorectal cancer who were working at the time they were diagnosed. These participants will be matched by gender and 5-year age group to a nationally representative sample of men and women from the general population. Participants in both groups will be followed over 12-months and have data collected on socio-demographic factors, work-related factors, and HRQoL while the cancer sample will have additional data collected on cancer treatment and symptoms, work productivity and cancer-related HRQoL.

### Aims and hypotheses

The key aims of the study are to:

1. Describe *transitions *in employment participation following a primary diagnosis of colorectal cancer within a 12-month period compared to individuals without cancer;

2. Identify the key factors influencing *work participation *during or after cancer treatment compared to individuals without cancer;

3. Identify the key factors influencing *time to work re-entry *after cancer treatment among individuals taking work leave for their cancer treatment;

4. Investigate the influence of changes in employment participation over a 12-month period on *HRQoL *at time 2 among individuals with cancer compared to those without cancer; and

5. Quantify the extent of *physical and cognitive limitations *at work (work disability) in individuals following a primary diagnosis of colorectal cancer.

We hypothesise that:

1. The proportion of middle-aged working adults with a primary diagnosis of colorectal cancer who substantially alter their work hours (i.e. by ≥20%) or stop working by 12 months after diagnosis will be more than 15% higher than among middle-aged working adults in the general community;

2. The key barriers to work participation or timely work re-entry after cancer will include regional or metastatic cancer at diagnosis, age, fatigue at six months, adjuvant therapy, living with an employed partner, limited work autonomy and low income; and,

3. Study participants who substantially reduce their work hours or leave the work force against their choice, will have clinically lower HRQoL scores at 12 months compared to those who remain employed at 12 months.

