### Data collection sources

Data will be collected during this project from four sources (Table 1):

**Table 1 T1:** Questionnaire item domains at each time point by cancer cases and general-population comparison group

	Cancer Group		Comparison Group
**Method**	**Telephone interview**	**Mailed questionnaire**	**Face-to-face interview**

Time 1^a^	1. Socio-demographics^b^ 2. Cancer treatments 3. Symptoms (MSAS^b^) 4. Work questions^a^ 5. Work limitations (WLQ)	6. Quality of life (SF-36)^b^ 7. Health behaviours & conditions^b^ 8. Cancer-specific quality of life (FACT-C) 9. Financial strain^b^	Question groups 1, 4, 6, 7, 8, 9 from HILDA Wave 9, 2009 data

Time 2	Repeat question groups 2-8		Question groups 1, 4, 6, 7, 8 from HILDA Wave 10, 2010 data

^a ^Time 1 for the Cancer Group occurs six-months after diagnosis however retrospective work questions are asked about their time of diagnosis (baseline) and about their current time (six months after diagnosis) therefore a common one year period will be compared across the cancer and comparison groups for key work questions.

^b^These questions are the same as those in the comparison group to enable direct comparison between groups.

Abbrevs: FACT-C = Functional Assessment in Cancer Therapy plus Colorectal Cancer module, HILDA = Household, Income and Labour Dynamics in Australia, MSAS = Memorial Symptom Assessment Scale, SF-36 = Medical Outcomes Study Short Form 36, WLQ = Work Limitations Questionnaire.

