#### 2) Telephone interviews (cancer group)

Participants with cancer will take part in structured telephone interviews at 6 and 12 months after diagnosis. At the 6-month data collection time point we will also ask participants to recall work-related information at the time they were diagnosed with cancer (baseline). Telephone interviews will be undertaken in order to maximise response rates, reach a wide geographical region and minimise participant burden, the latter being important in a working population that may require out-of-hours contact. Interviews will be conducted by trained and experienced interviewers. To minimise respondent burden, interviews will be kept to approximately 30 minutes each. A flexible interview schedule will be adopted and tailored to suit the schedules of working participants.

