### Specific questionnaire items and measures

*Generic baseline socio-demographic information*for the cancer and comparison groups will include items on age, gender, education level, country of birth, culture, marital status, household income, health and other insurances, postcode of residence, number and age of children.

*Participants' work situations, generic HRQoL, health behaviours and conditions*will be collected at both time-points (Table 1) with identical items for the cancer and comparison groups. Work situation items include a compilation of validated tools from Australian government surveys (eg Australian Bureau of Statistics (ABS) Labour Force Survey, ABS 1999 Survey of Living Standards) and ask about: employment status, usual and preferred weekly hours, reasons for working part time, occupation, occupation change, industry, trade union membership, paid sick leave, paid holiday leave, expected resignation or dismissal, supervisory responsibilities, employer type, workplace size, job satisfaction, if the respondent has a disability, type of disability, disability commenced in the last year, impact of disability on work probability, financial strain (e.g., access to emergency funds, bills paid late), intended age of retirement and intentions of stopping work during next three years. Generic HRQoL will be evaluated using the widely-used and validated Medical Outcomes Survey Short Form (SF-36). Physical activity estimates will be obtained via the International Physical Activity Questionnaire (short-form) [19]. Other standard health behaviours and conditions (smoking, alcohol consumption, height, weight and chronic illnesses) will also be asked.

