### Analyses

All analyses will include gender as a factor and will test for interactions of gender with other factors in the model. Gender differences are important, as not only do men and women have different work participation rates, work hours and occupation types in the general population [17], they respond and adjust differently to illnesses, have different health behaviours and other risk factors for cancer [24]. Where no effect modification is observed, pooled results will be presented. Socio-demographic characteristics will be compared at baseline to identify any statistically significant differences between the cancer and comparison groups. Descriptive analyses will be conducted to chart employment transitions over the year since diagnosis among the cancer group and over 2009-2010 year period among the comparison group. Although the first time point for the cancer group is six months after diagnosis, participants are asked to recall work circumstances (occupation type, hours worked, industry etc) at the time of diagnosis (retrospectively) and at time 1 (six months after diagnosis). Separate multivariable logistic regression modelling will identify explanatory variables that are significantly associated with work participation in the cancer and comparison groups. For these models, adjusted odds ratios with 95% confidence intervals and p-values will be computed. Cox proportional hazards models will assess time to work resumption in the participants with cancer and significant correlates of timely work re-entry. Mixed-effects modelling for the cancer group will be used to examine change in HRQoL scores (time 1 - time 2) by participants who reduce or leave in that time versus those who do not. We will also compare HRQoL scores between the cancer and comparison groups at time 2. Data on work limitations measured in the cancer group will be scored across the four domains and mixed-effects modelling undertaken to assess changes in scores between time 1 and time 2. Reasons for study withdrawal in the cancer sample will be closely monitored. Descriptive analyses of baseline variables for the 'completers' and 'non-completers' will identify any possible bias and the source and, if necessary, subsequent analyses will be weighted accordingly. In the comparison group, only responders at both HILDA Waves 9 and 10 will be included.

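### Six-month fatigue is named as a barrier to timely work re-entry, but for patients already back at work by then it is measured after the event, which exposes the Cox estimate to reverse causation

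*Protocol article*

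**What the plan says.** All references are to the protocol article.

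- **Aims and hypotheses.** Hypothesis 2 gives one list of expected barriers to work participation or timely re-entry: "regional or metastatic cancer at diagnosis, age, fatigue at six months, adjuvant therapy, living with an employed partner, limited work autonomy and low income". The six-month timing of fatigue is part of the hypothesis. Aim 3 concerns time to re-entry among people who took leave for treatment.
- **Analyses, re-entry.** "Cox proportional hazards models will assess time to work resumption in the participants with cancer and significant correlates of timely work re-entry".
- **Analyses, participation.** "Separate multivariable logistic regression modelling will identify explanatory variables that are significantly associated with work participation in the cancer and comparison groups".
- **Telephone interviews.** "Participants with cancer will take part in structured telephone interviews at 6 and 12 months after diagnosis". No earlier contact for data collection is described.
- **Data collection sources, Table 1.** Symptoms (MSAS) and socio-demographics are both placed at Time 1, which for cases is six months. At Time 2 the entry is "Repeat question groups 2-8", so socio-demographics (group 1) are not asked again.
- **Recall to diagnosis.** This covers work items: "participants are asked to recall work circumstances (occupation type, hours worked, industry etc) at the time of diagnosis (retrospectively) and at time 1". Symptoms and household income are not named.
- **Specific questionnaire items and measures.** Household income belongs to the socio-demographic block ("education level, country of birth, culture, marital status, household income, health and other insurances"), which that section labels as baseline.
- **Analyses, last paragraph.** A two-stage simultaneous probit least squares model, in which health status is endogenous to work participation, is added to complement the other models.

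**The concern.** A fixed covariate in a Cox model should be known before the event it is used to explain. A patient who resumed work in month 3 reports fatigue in month 6, with three months of work already behind them. If being back at work, or whatever accompanies it, changes the fatigue reported at month 6, the model reads that difference as fatigue having delayed or hastened the return.

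This matters because hypothesis 2 speaks of barriers, the aims speak of factors that influence work, and the Discussion intends to pass the barriers on to supportive-care providers. The Discussion also faults earlier studies for retrospective or cross-sectional designs. A covariate measured after the event brings part of that weakness back.

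**Working it through.** **Step 1. Time order, variable by variable**

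| Variable | When it is known | Cox model, time to re-entry | Logistic model, 12-month participation |
|---|---|---|---|
| Stage, age, gender | Diagnosis | Sound | Sound |
| Recalled work characteristics | Diagnosis, by recall | Sound in time order | Sound in time order |
| Fatigue | Six months, fixed by hypothesis 2 | After the event for anyone back before six months | Before 12-month status, but after the change for anyone who stopped or altered work earlier and stayed so |
| Household income | Time 1 by Table 1; reference date unclear | As fatigue, if it refers to Time 1 | As fatigue, if it refers to Time 1 |

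The Background says only that most people return within 12 months of taking leave. The share back before six months is not given, so the size cannot be derived from the document.

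**Step 2. Illustration on assumed inputs**

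The plan states no figure on this point, so there is none to reproduce. Assumptions:

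- n = 125, the protocol's target for cases retained at 12 months, all treated as on leave. The number who take leave is not given.
- Exponential return times with a share p6 back by six months: λ = −ln(1 − p6)/6 per month. For p6 = 0.3, 0.5 and 0.7, λ = 0.059, 0.116 and 0.201. Censoring at 12 months.
- Six-month fatigue has no effect on return (true HR = OR = 1). A latent normal score is raised by δ SD in those not back at six months and cut at zero. The share fatigued is then 50% in those back, and Φ(0.25) = 60% or Φ(0.5) = 69% in those not back.
- 300 runs per row. Monte Carlo standard error at a true 5% rejection rate: √(0.05 × 0.95/300) = 1.3 points.

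Median estimates, with the percentage of runs significant at 5%:

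| p6 | δ | Cox, full period: HR (%) | Logistic, not working at 12 months: OR (%) | Landmark Cox from six months: HR (%) | At risk at landmark |
|---|---|---|---|---|---|
| 0.3 | 0 | 1.01 (5.7) | 1.02 (5.7) | 0.98 (3.7) | 88 |
| 0.3 | 0.25 | 0.81 (13.3) | 1.30 (10.3) | 0.98 (5.7) | 88 |
| 0.3 | 0.5 | 0.69 (33.7) | 1.56 (23.3) | 1.05 (4.3) | 88 |
| 0.5 | 0 | 0.99 (6.0) | 1.02 (3.7) | 1.03 (8.3) | 62 |
| 0.5 | 0.25 | 0.83 (12.0) | 1.33 (7.3) | 0.98 (4.7) | 62 |
| 0.5 | 0.5 | 0.70 (39.0) | 1.68 (22.3) | 1.03 (4.0) | 62 |
| 0.7 | 0 | 0.98 (5.7) | 1.05 (3.7) | 0.96 (7.0) | 38 |
| 0.7 | 0.25 | 0.86 (13.0) | 1.36 (2.7) | 1.02 (2.3) | 38 |
| 0.7 | 0.5 | 0.72 (39.0) | 1.93 (6.0) | 0.97 (5.3) | 38 |

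The δ = 0 rows are the control: without a reverse shift the full-period Cox model is close to 1. Some logistic fits gave convergence warnings. At p6 = 0.7 only about 125 × 0.3² = 11 people are still off work at 12 months, so those logistic entries are rough.

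**Step 3. A second set-up**

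Here 100 patients are on leave, fatigue is continuous, and it is 0.25-0.5 SD lower in those already back. Return hazards of 0.08, 0.12 and 0.18 per month give 1 − exp(−6λ) = 38%, 51% and 66% back by six months. The full-period Cox HR is 0.79-0.90 per SD, with 14-51% of runs significant. The landmark HR is 0.99-1.01, with 3-6% significant.

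Both set-ups show a spurious barrier in the full-period model, and in both the landmark removes it.

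**The case against.** **The Cox covariates are not listed.** Hypothesis 2 gives one pooled list for two outcomes, and an article may leave risk-set details to an analysis plan. This has some force: the article does not say that fatigue will enter the Cox model as a fixed covariate for everyone. But hypothesis 2 names six-month fatigue as a barrier to timely re-entry, and the Cox model is the only analysis of re-entry described. Nothing in the text keeps early returners out of that comparison.

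**Endogeneity is already addressed.** The two-stage model does recognise that health and work determine each other. It concerns work participation, complements rather than replaces the other models, and covers neither time to re-entry nor income.

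**The size and direction are assumed.** This stands. If resuming work raises fatigue, the bias runs the other way. If recovery drives both lower fatigue and early return, part of the association is the one hypothesised. A value taken after the return cannot separate these.

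**A reader might infer more than the document supports:**
- *That the logistic models are compromised in general.* Six-month covariates precede 12-month status. Only people who changed work before six months and stayed so are affected.
- *That income is certainly measured too late.* Table 1 points to Time 1, but the block is labelled baseline, a word the article uses both for diagnosis and for an interview.
- *That partner employment has the same fault.* No such item is listed, and there is no evident route from a patient's return to a partner's job.
- *That adjuvant therapy is misclassified over time.* Neither its coding nor the Cox time origin is stated, and aim 3 refers to re-entry after treatment.

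**Conclusion.** The point holds for six-month fatigue in the analysis of time to re-entry. The document itself fixes the time of measurement, and anyone back at work earlier has a covariate recorded after the event. The plan is exposed to reverse causation; how much occurs cannot be read from it. Under no true effect and the assumed inputs, the two set-ups together give spurious hazard ratios of 0.69-0.90 and false-positive rates of 12-51%. The two hazard-ratio scales differ: one is fatigued against not fatigued, the other is per SD. These are illustrations, not forecasts.

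The same concern applies more narrowly to the logistic models (3-23% of runs significant in the shifted rows). It applies to household income only if income is recorded as at Time 1.

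**What to change.** 1. **Full-period Cox model:** use only variables fixed at diagnosis, namely stage, age, gender and the recalled work characteristics.
2. **Time 1 measures, including fatigue:** test them in a landmark Cox model among patients still off work at Time 1, with time counted from that interview. Word hypothesis 2 so that fatigue refers to re-entry after six months.
3. **Household income:** ask it with reference to the time of diagnosis, beside the work items already recalled, and state that reference date.
4. **Logistic models:** add a sensitivity analysis limited to changes after Time 1. Keep the full 12-month analysis, because aim 2 also covers participation during treatment and a restricted analysis would drop those who stopped early.

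**Cost:** changes to the analysis wording and the income question. The landmark model uses fewer patients (about 38-88 of 125 in the first illustration and 34-62 of 100 in the second), so fatigue is estimated less precisely and says nothing about returns before six months. Income at diagnosis would rest on recall, as the work items already do.
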